**Figure 4 F4:**

Screening and enrollment process.

If the participant was randomized to either of the web-based training groups, a user name and password was automatically generated and sent to the participant’s email. Participants in the two web-based training groups had a five-week window to complete the web training modules at their own pace and in any order before being prompted to complete the midpoint assessment. When the midpoint assessment was due, access to the web training was suspended until the assessment was completed. After completion, the web training was again made available. The midpoint assessment included an evaluation of the training and assessment of knowledge (which also served as the CE quiz). This midpoint assessment also served as a trigger for the web-based training plus supervision group to begin supervision calls. Participants randomized to web-based training (without supervision) were allowed continued access to the training materials but had no other additional contact until the end of the six-week supervision period. Participants randomized to web-based training plus supervision began scheduling regular supervision calls over a six-week period. At the completion of the six-week supervision period, participants in all three groups were contacted by email to begin scheduling the second SPI (Time 2). Immediately following completion of the second SPI all participants were sent an email directing them to the web-based post-training assessment. Completion of the post-training assessment concluded study participation. At this point, training-as-usual (control) group participants were provided access to the training and were offered the opportunity to complete the CE questionnaire for credits. This overall process is illustrated in Figure 5. Ethical review and approval for the study was provided by the Stanford University and NERI Institutional Review Boards and the VA Palo Alto Health Care System Research and Development committee.

**Figure 5 F5:**

Study design.

### Assessment methods

#### Evaluation strategy and procedures

Assessment of effectiveness of online training is intrinsically challenging. Assessment methods in large healthcare systems must be easily implemented, relatively brief in duration, and scalable at modest cost to reach large numbers of geographically-distributed providers. In the current study, online self-report questionnaire methodology provided a relatively simple way of assessing results of training for a large number of mental health providers. Three core domains of outcome were measured: knowledge assessed through multiple-choice tests; self-reports of perceived self-efficacy in technique application; and to assess implementation of CBT techniques, self-reported frequency of application with PTSD patients. The content of web-based data collection and the assessment time points are shown in Figure 6.

**Figure 6 F6:**
[figure not shown]
Web-based research measures.

While self-report instruments can assess knowledge, perceived self-efficacy, and participant-perceived degree of use of CBT techniques, they are limited in their ability to examine actual skills development. The latter outcome is, of course, especially important in evaluating the success of training. To assess actual mastery of therapy skills, our primary outcome measure was based on simulated treatment-delivery interviews with standardized patients. Standardized patients have been used widely in medical settings to teach and measure skills of assessment and diagnosis [27,28]. This methodology has rarely been used to examine intervention skills. However, a small but growing literature exists for the use of standardized patients in mental health training, particularly to evaluate clinical interviewing for substance abuse [29,30]. We conducted the standardized patient interview sessions over the phone, to facilitate assessment of mental health providers located across the country. This combination of online and telephone assessment methodologies was deemed practical to deliver and complementary in terms of information yield.

#### Standardized patient (SP) interview methodology

Measurement of participant performance in simulated sessions with the standardized patient was used to assess actual skills acquisition. The goal was to create an assessment protocol that ensured standardization of stimulus conditions while permitting actors in the standardized patient role to respond with considerable flexibility depending upon which of a wide range of provider behaviors occurred. The standardized patient interviews were conducted at baseline and follow-up for all participants.

Participants received email orientation materials 72 h prior to their interview. This orientation included a brief description of procedures for the standardized patient interview, description of the clinical background of the patient, information about the time and date of the phone interview, and the phone number at which they would be contacted. 24 h prior to the scheduled interview, the actor was instructed to call the participant and remind him or her to read the materials and confirm when the interview would take place. If the participant did not answer this call, the actor was instructed to leave a voicemail or a message with the receptionist if voicemail was not available.

Simulated interviews were conducted during 50-minute telephone calls. The 50-minute sessions were divided into a five-minute introduction/orientation followed by three 15-minute segments (one for each intervention). We defined a segment as a portion of the standardized patient interview that could be rated according to study criteria.

To ensure a uniform set of stimulus conditions, a scripted approach to the simulated interviews was developed. Upon initiation of the interview, scripted actor statements were used to orient the participant to the process, and ensure readiness to participate in the interview (*e.g.*, to ensure that the participant had read the patient background material, and was located in a quiet environment with relative protection from interruption). Standardized scripts were also used to open the three segments. In this way, it was possible to convey standard presentations across conditions and actors and provide participants with standardized opportunities to demonstrate appropriate techniques. Because of the potential for variation in participant behavior, conditional responses (Figure 7) were developed to guide actor response after the opening statements. The rules were kept relatively simple in order to avoid overloading the actor with performance demands.

**Figure 7 F7:**
[figure not shown]
Example conditional responses from standardized script.

Effective actor selection and training were critical to ensure authenticity of the interaction. To ensure that actors were familiar with the clinical presentation of PTSD in veteran patients, clinical psychology graduate students were interviewed for potential participation. Those selected had typically worked in a VHA practicum setting and performed well on a practice role play that was part of the selection process.

Actors were given a manual describing the interview procedures. The manual included background information about the patient they would portray, an overview of the procedures for the interview, a telephone script for the one-day reminder phone call about the interview, the interview script (including general instructions and scripted statements), conditional responses, and technical instructions for audio recording the interview. Background information about the patient was intended to provide the actors with enough information to complete their interactions with participants in a manner consistent with natural therapeutic conversation and allowing flexible responses to questions. Background description included details of personal history, medical history, symptom display, reasons for seeking help, personality (*i.e.*, response style), affective presentation, and general disposition; these areas were covered in anticipation of possible questions and statements produced by participants. Actor training sessions were held in close time proximity to the conduct of the interviews. Each actor completed a two-day intensive in-person training workshop where they were given an overview of the study protocol, watched video footage of veterans with PTSD, participated in a question-and-answer session with a veteran who had recently graduated from a local inpatient PTSD program, reviewed the protocol for each segment of the interview, and then participated in numerous role-plays. Actor trainees were given significant opportunity to practice each of the techniques in the simulated interview and receive feedback on their performances. They worked as a team during practice sessions to observe one another’s performances and decide if any alterations needed to be made to the standardized patient protocol.

After it was judged that the standardized patient protocol and actor performances were adequate, ‘dress rehearsals’ were conducted in which the actors called study personnel who played the role of study participants. Actors were required to demonstrate their fidelity to the interview structure as well as ability to successfully record the session and deliver the recording to the study manager.

The script developed for the standardized patient interview included instructions for the conduct of the interview, and an outline of the clinical details and instructions for each of the three interview techniques (motivational interviewing, goal-setting, behavioral task assignment). Furthermore, opening statements were scripted to begin each of the segments. In the case of motivational interviewing, two additional scripted statements were included to provide opportunities for participants to respond to deliberate change and counter-change statements. Conditional responses were designed to facilitate anticipated techniques taught in each of the respective modules. To maintain consistency, the actors were trained to identify and respond to some of the specific techniques with scripted responses. For example, in the motivational interviewing module, participants were taught to use a decisional balance sheet exercise (Figure 8), and actors were trained on the conditional responses illustrated in Figure 7**.** Actors were blind to the condition to which the participant was assigned.

**Figure 8 F8:**
[figure not shown]
Decisional balance interactive exercise.

#### Rating of simulated interview performances

Raters were graduate student research staff not delivering the intervention, all of whom were masked to study condition and time point of assessment. Five practice transcrips were rated independently and discussed as a group to identify points of convergence and divergence. Decisions about rating disagreements were reached and clarifications were added to the rating guide. Once rating began, 20% of all transcripts were randomly selected to be re-rated by a second rater. Raters were masked as to which transcripts were being re-rated.

For each of the CBT techniques, raters scored transcripts based on the degree to which specific technique-related participant behaviors were observed. Each behavior was rated as ‘0’ (Does Not Employ), ‘1’ (Partially Employs), or ‘2’ (Consistently Employs). Behavioral criteria for the three rating levels guided raters. For motivational interviewing, goal-setting, and behavioral task assignment, 17, 8, and 15 behaviors, respectively, were rated. Examples of techniques for behavioral task assignment were ‘frame as an experiment’ and ‘generate potential tasks.’ For each of the three techniques, raters also scored ‘overall degree of collaboration’ (0 to 4) and ‘overall effectiveness’ with the techniques (0 to 4).

#### Statistical analysis plans

##### Primary analyses

The primary outcome of the study intervention is the performance of participants in demonstrating CBT techniques during the SPI assessment at post-training. Summary scores for each of the CBT techniques will be constructed from the ratings of the SPIs and the properties of the scores evaluated. The analyses to be performed will compare the performance of participants in the training-as-usual (control) and web-based training groups using the analysis of covariance (ANCOVA) comparing the average post-test scores among the three training groups, adjusting for baseline scores [31]. We hypothesize that participants in the web-based training groups will exhibit greater improvement in skills performance than those in the training-as-usual (control) group. We also hypothesize that web-based training plus supervision will be associated with greater skills improvement than web-based training alone. If the null hypothesis of no difference among the three groups is rejected, we will compute pre-planned comparisons of the scores between the individual groups adjusting for multiple comparisons. All participants will be analyzed in the training group to which they were randomly assigned, regardless of their compliance with the assigned training method and the assessments. Participants who do not complete the post-training SPI will be considered to have the same value at post-test as at baseline. To assess sensitivity of our results to potential response bias due to more ‘successful’ trainees completing the follow-up assessment, we assumed that non-completers made no change from baseline (last observation carried forward). This is a commonly used method of imputation when doing this type of sensitivity analysis.

Analyses focusing on the intent-to-train sample will also be repeated for the sample of participants who completed ‘therapeutic doses’ of the training interventions. To meet the criterion for completion of the web portion of the training, a participant will have to complete 75% of each of the three modules. To complete the web-based training plus supervision process, a participant will have to complete 75% of each of the online modules and attend three or more of the supervision sessions.

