**Figure 3 F3:**
[figure not shown]
Recruitment postcard.

Once consented, participants were randomly assigned to one of three study conditions: web-based training plus supervision, web-based training, and training-as-usual (control). Participants who completed the baseline assessment, including the simulated patient interview, were stratified by self-reported previous CBT experience and randomized to one of the three training groups. We used permuted blocks of nine participants within each stratum. The control group clinician participants were free to participate in any training activities they would otherwise receive, including local continuing education activities, conference participation, or other formal training programs taking place in the VA. Participants were stratified on the basis of self-rated degree of expertise in cognitive-behavioral therapy (low = none or beginner; high = intermediate, advanced, or expert) and were randomized within strata to one of the three training groups (See Table 1)**.**

**Table 1 T1:** Stratified random group assignment

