	**Self-rated CBT expertise**	
**Random Group Assignment**	Low	High
Training-as-usual	19	37
Web-based training only	21	36
Web-based training +expert supervision	19	36

In this study, a web-based screening instrument was developed and made available through a recruitment registration website announced on flyers and in recruitment emails. Participants accessed the online screener that determined eligibility for the study. Individuals were excluded if they: were not a full-time VHA or Vet Center employee; were not a clinical psychologist, social worker, psychiatrist, readjustment counselor, mental health counselor, substance abuse counselor, nurse, psychology trainee, or a trainee classified as ‘other’; were not currently counseling/treating patients with PTSD as part of their VHA or vet center clinical work; or had previously completed VHA-offered training in cognitive-behavioral therapy for depression (whose content domains overlapped significantly with web module content).

Those eligible were directed to an online informed consent process. If consent was completed (requiring two online signatures), the baseline assessment instrument was made available. Those not eligible were thanked and informed that they were not eligible for the study. A web-based baseline assessment was administered to determine baseline knowledge and perceived self-efficacy. In addition, participants had to schedule and complete a standardized patient interview (SPI, Time 1, discussed below). Both the baseline assessment and SPI were required prior to randomization and access to the web training. Randomization to one of the three groups occurred once the participant was identified as having completed the SPI. This process is illustrated in Figure 4.

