##### Secondary analyses

We also hypothesize that providers in the web-based training groups will show significantly greater improvement in CBT-related knowledge, perceived self-efficacy, and self-reported implementation of CBT techniques than those in the training-as-usual (control) group. The baseline and post-test assessments consist of multiple choice knowledge items, perceived self-efficacy, and practice behavior variables. As with the SPI scores, summary scores will be calculated from the individual questions. Treatment groups will be compared using ANCOVA on the post-test scores controlling for the baseline scores with follow-up comparisons as described above. Moderator analyses are not planned given the use of a randomized trial for testing the primary and secondary hypotheses of the study.

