##### Power analysis

Power calculations were computed based on the estimated percentage of participants who would successfully implement the techniques as assessed by the SPI. These calculations indicated that 40 participants per group (total n = 120) would provide 79% power to detect a rate of successful implementation of 48% in the web-based training (without supervision) group compared to 15% in the training-as-usual (control) group, and 91% power to detect a rate of 54% in the web-based training plus supervision group compared to 15% in the training-as-usual (control) group, both at the 2.5% significance level.

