## Results and discussion

In this paper, we present evidence for the effectiveness of our study recruitment procedures. As shown in the flowchart of recruitment and study completion in Figure 9, we exceeded our recruitment goals. The study protocol called for recruitment of an approximate target of 135 mental health providers; in fact we were able to randomize 168 participants for the study, ahead of the planned recruitment pace. In keeping with the overall composition of VHA mental health providers, our sample was predominantly white (79%), female (70%), and had post-graduate training in psychology, social work, nursing or psychiatry. The average age was 49, and more than 90% had post-graduate qualifications (Master’s or Doctoral level).

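### Randomisation is stratified by self-rated CBT expertise, but the stated ANCOVAs name only the baseline score; adding the stratum is a nearly free improvement

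*Protocol article*

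**What the plan says.** **Design.** Under Recruitment and randomization, the protocol article states: "Participants were stratified on the basis of self-rated degree of expertise in cognitive-behavioral therapy". Low means none or beginner; high means intermediate, advanced or expert. On the allocation method it says: "We used permuted blocks of nine participants within each stratum". Table 1 gives the resulting counts by group and stratum.

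**Primary analysis.** The model is an ANCOVA on the post-training standardized patient interview (SPI) scores, "comparing the average post-test scores among the three training groups, adjusting for baseline scores". Comparisons between individual groups follow only if the three-group null hypothesis is rejected.

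**Secondary analyses.** For knowledge, perceived self-efficacy and self-reported practice: "Treatment groups will be compared using ANCOVA on the post-test scores controlling for the baseline scores".

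Nothing in the article places the expertise stratum in any of these models.

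**The concern.** Blocking within strata removes most of the chance difference between arms in CBT expertise, so the treatment contrast varies less from one randomisation to the next. A model without the stratum leaves the variation due to expertise in the residual and computes its standard error as if the arms could still differ by chance on expertise. If expertise predicts the post-test score given the baseline score, that standard error is too large, the confidence intervals are too wide and the tests reject less often than their nominal level.

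This matters most at the gate in the primary analysis, because a conservative three-group test makes the pairwise comparisons harder to reach. The contrast between the two web-based arms is the narrowest in planning terms (54% against 48%), and the Power analysis section gives no power for it.

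**Working it through.** **1. Inputs from the article.** Table 1, low/high:
- training-as-usual 19/37 (n = 56)
- web-based training 21/36 (n = 57)
- web-based training plus supervision 19/36 (n = 55)

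Totals: low 19 + 21 + 19 = 59; high 37 + 36 + 36 = 109; 59 + 109 = 168, which agrees with the number randomised. The share in the low stratum is 34%, 37% and 35% by arm.

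**2. The plan's own power figures.** The plan has "40 participants per group (total n = 120") and two comparisons with control, "both at the 2.5% significance level". The exact power of a two-sided Fisher test at 0.025 with 40 per group is 78.8% for 48% against 15%, and 91.3% for 54% against 15%. The stated 79% and 91% therefore reproduce. They compare proportions and use neither the baseline score nor the stratum, so this point does not affect them. They serve below only as reference levels.

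**3. Assumed input.** The partial R² of the stratum given the baseline score is not in the article. I use 0.02 to 0.10 as the working range.

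**4. Size of the standard-error excess and of the power difference.**
- Excess in the reported standard error = 1/√(1 − R²) − 1.
- Power with the stratum = Φ[(z₀.₉₈₇₅ + z_power)/√(1 − R²) − z₀.₉₈₇₅], with z₀.₉₈₇₅ = 2.241, z₀.₇₉ = 0.806 and z₀.₉₁ = 1.341.

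| Assumed R² | SE too large by | 79% becomes | 91% becomes |
|---|---|---|---|
| 0 | 0.0% | 79.0% | 91.0% |
| 0.02 | 1.0% | 79.9% | 91.6% |
| 0.05 | 2.6% | 81.2% | 92.4% |
| 0.10 | 5.4% | 83.4% | 93.8% |

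This formula gives the test statistic unit variance in both models. Under stratified blocks, the statistic from the baseline-only model varies less than that, so the power columns are upper figures. Allowing for it, power with the stratum is Φ[z₀.₉₈₇₅/√(1 − R²) + z_power − z₀.₉₈₇₅]. The 79% then becomes 79.7%, 80.6% and 82.3% at R² = 0.02, 0.05 and 0.10.

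**5. Cost of adding the stratum.** From the Table 1 counts, the variance inflation due to imbalance is at most 1.0006 (web-based training against control), plus one degree of freedom.

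**6. Simulation of the design.** There were 4,000 runs per row, with N = 168 (59 low, 109 high), blocks of nine within strata, no group effect, an assumed baseline/post-test correlation of 0.5, and a three-group F test at 5%. The effect of expertise is its effect on the post-test score beyond baseline, in SD units.

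| Effect of expertise | Mean SE without / with stratum | SE excess | Rejection rate without / with |
|---|---|---|---|
| 0 | 0.1636 / 0.1636 | 0.0% | 5.4% / 5.4% |
| 0.25 | 0.1655 / 0.1640 | 0.9% | 4.1% / 4.1% |
| 0.5 | 0.1702 / 0.1644 | 3.6% | 3.9% / 4.9% |
| 1.0 | 0.1861 / 0.1636 | 13.7% | 2.5% / 5.3% |

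The Monte Carlo standard error near 5% is √(0.05 × 0.95/4000) = 0.34 points, so only the lower rows show a clear difference in rejection rate. At the 1.0 SD effect, the true spread of the estimate was 0.165 without the stratum and 0.164 with it. The reported standard error is overstated; the estimate is almost as precise either way.

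**The case against.** **The article is a condensed account, and the full analysis plan may list the stratum.** That is possible. But the article is not silent on covariates: it states the model and its adjustment variable twice, and the stratum appears in neither statement. The point concerns the analysis as stated. If a fuller plan already includes the stratum, the point is met.

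**The baseline score may already carry what expertise would add.** This is a fair point and it stands. For the primary outcome, the baseline covariate is an observed rating of the same skills, whereas the stratum is a two-level collapse of a self-rating. On the other side, each technique is rated from one 15-minute segment, and the Discussion says that most measures were study-specific and not validated, so an imperfect baseline could leave something for expertise to predict. The article settles neither view, so the claim has to stay conditional.

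**The effect is small and on the safe side.** This also stands. Arms are closely balanced on the stratum, and 168 were randomised against 120 in the power calculation.

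**Stronger readings to avoid.** A reader might infer that precision bought by stratifying is lost. It is not: the balance is delivered whichever model is fitted, as the 0.165 against 0.164 comparison shows. A reader might also infer that the analysis is invalid because it does not mirror the design. A baseline-adjusted ANCOVA by assigned group remains valid here, if possibly conservative.

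**Conclusion.** The point holds as a minor, conditional one about efficiency. The stated primary and secondary ANCOVAs leave out the factor used to stratify the randomisation. If expertise predicts the post-test score beyond baseline, the reported standard errors are too large and the tests conservative. At an assumed partial R² of 0.02 to 0.10, the excess is about 1% to 5%, and the loss of power about 1 to 4 points at most against the 79% reference level. At zero, nothing changes. The R² range is an assumption, because the article reports no association between expertise and any outcome.

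There is no bias and no inflation of type I error, so a finding of benefit from the stated model would not be made unsafe. The documents do not support saying outright that the standard errors are too large.

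**What to change.** Enter the low/high self-rated expertise stratum as a fixed factor, beside the baseline score, in every primary and secondary ANCOVA and in the pairwise comparisons that follow from them; otherwise state why it is left out. The cost is one degree of freedom and negligible variance inflation, and no new data are needed because the stratum was recorded before randomisation for all 168. No matching change is needed for missing post-training interviews: the plan carries the baseline value forward, so there is no imputation model to which the stratum could be added.

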### Rationale for selection of core training modules

The CBT techniques were divided into three training modules: motivational interviewing; goal-setting; and behavioral task assignment. These modules were selected for multiple reasons. First, all three modules focus on the essential need to prompt behavior change in those seeking treatment services. Second, they represent behavior change skills that can be trained with relatively brief investment of time and effort for potentially large yield in clinical performance and outcomes. These core techniques and practices are typically embedded in multi-session CBT package interventions, which made conversion to web-based training format readily feasible for the current study. Third, the modules we selected focus on generic, multi-purpose CBT techniques, which can be broadly applied across a wide range of behavior change targets. Finally, these techniques can be integrated by diverse providers into ongoing therapy sessions flexibly and immediately. The practices to be disseminated were also considered to ‘fit’ well within existing structures of PTSD care within VHA (*e.g.*, time-limited approaches), an important consideration in dissemination, and to reflect expressed training interests among PTSD treatment providers who participated in focus groups. Generally, the three techniques have not been studied as stand-alone interventions for PTSD, and they are not designed to represent comprehensive PTSD interventions. Motivational interviewing has been used successfully to increase motivation to change a range of behaviors that co-occur with PTSD, whereas goal-setting and behavioral task assignment are components of existing evidence-based PTSD protocols (*e.g.*, prolonged exposure and cognitive processing therapy), as well as interventions for other trauma-associated problems.

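### Within each score, adjusting the pairwise tests after the three-group F test has already gated them is not needed for error control and can only lower power

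*Protocol article*

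**What the plan says.** In the protocol article, under Statistical analysis plans, Primary analyses:

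- The main test is an ANCOVA "comparing the average post-test scores among the three training groups, adjusting for baseline scores".
- The pairwise step has two conditions in one sentence. It is reached only if the three-group null hypothesis "is rejected, we will compute pre-planned comparisons of the scores between the individual groups adjusting for multiple comparisons". So the comparisons are gated and also adjusted. The adjustment method and the level of the F test are not named.
- Both web arms are expected to beat control. A further stated hypothesis is that "web-based training plus supervision will be associated with greater skills improvement than web-based training alone". All three pairs are therefore of interest.
- The outcome is not one score: "Summary scores for each of the CBT techniques will be constructed from the ratings of the SPIs", and there are three techniques. The adjustment is attached to comparisons between groups. No rule across scores is described.

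Secondary analyses carries the scheme over to knowledge, self-efficacy and self-reported practice: ANCOVA "controlling for the baseline scores with follow-up comparisons as described above".

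Power analysis uses 2.5% for each of the two comparisons with control, has no gate, and gives no power for supervision versus web alone.

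**The concern.** A gate and a multiplicity adjustment are two ways of paying for the same three comparisons. With four or more groups the gate alone would not be enough, and a second step would be justified. With three groups it is enough within a score, so the adjustment leaves part of the 5% unused. The price is power for detecting pairwise differences. It falls mainly on supervision versus web alone, which is a stated hypothesis with no planned power, and on web versus control if the true effect is moderate.

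**Working it through.** **The plan's own figure.** Inputs from Power analysis: 40 per group, 48% and 54% against 15%, level 2.5%. Exact power of the two-sided Fisher test is 78.8% and 91.3%, which reproduces the stated 79% and 91%. Sidedness is not stated; two-sided fits. These figures concern single ungated comparisons of proportions, so they do not describe the gated score analysis.

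**Error control within one score.** Call the means C, W and S. The pairwise nulls are C=W, C=S and W=S. If any two hold, so does the third, so the only intersection hypothesis is C=W=S, and the F test tests it. Closed testing then allows each pairwise null to be rejected when both the F test and that pair's own test reject at 5%. Two cases remain:

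- All three equal: an error requires the F test to reject, so its probability is at most 5%.
- Exactly one pair equal: only one true null exists, and its own test errs at most 5% of the time.

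Simulation at 56/57/55 (Table 1 of the article; F test at 5% assumed) agrees. The gate alone gives 5.0% to 5.1% under the complete null and 5.0% with one equal pair. Gate plus Bonferroni over three pairs uses about 4.2% and 1.7%; the second figure is simply 5%/3 once the gate is passed.

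**Power, moderate effects.** Assumed: effects against control of 0.4 SD (web) and 0.6 SD (supervision), baseline correlation r = 0.5.

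- Residual SD = √(1 − 0.5²) = 0.866. Residual df = 168 − 4 = 164.
- Web versus control: (0.4/0.866) / √(1/56 + 1/57) = 0.462/0.188 = 2.455.
- Supervision versus web: (0.2/0.866) / √(1/57 + 1/55) = 0.231/0.189 = 1.222.
- Critical t values: 1.974 (5%), 2.262 (2.5%), 2.419 (1.67%).
- Approximate power = Φ(shift − critical value). Web versus control: Φ(0.48) = 68%, Φ(0.19) = 58%, Φ(0.04) = 51%. Supervision versus web: Φ(−0.75) = 23%, Φ(−1.04) = 15%, Φ(−1.20) = 12%.

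Simulation including the gate gives:

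| Pairwise rule after the gate | Web vs control | Supervision vs web |
|---|---|---|
| Unadjusted 5% | 68% | 23% |
| Holm | 59% | 18% |
| 2.5% level | 58% | 15% |
| Bonferroni, three pairs | 52% | 12% |

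The loss is 68 − 59 = 9 to 68 − 52 = 16 points for web versus control, and 23 − 18 = 5 to 23 − 12 = 11 points for supervision versus web. Supervision versus control changes little: 91.6% against 89.1% under Bonferroni at 56 per arm.

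**Power, effects near the design rates.** On an assumed latent-normal scale, 48% and 54% against 15% correspond to about 0.99 and 1.14 SD. Gate plus Bonferroni then still has at least 99.8% power for both comparisons with control at 56/57/55. Supervision versus web is a difference of 1.14 − 0.99 = 0.15 SD, with about 15% power under the gate alone and 7% under Bonferroni.

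**Across the three scores.** If each score is gated at 5%, the scores are independent, and each has one true pairwise null behind a gate that is certain to open, the chance of at least one false pairwise claim is 1 − 0.95³ = 14.3%. Under the complete null, simulation with the gate alone gives 14.1% for independent scores and 8.5% for a correlation of 0.9.

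**The case against.** A reader might infer that the gate alone controls the error rate of the primary outcome, so that the adjustment buys nothing at all. The documents do not support that. There are three technique scores, and the gate works score by score. If both web arms work equally well on three independent scores, the pairwise adjustment happens to cut the error across scores from 14.3% to 1 − (1 − 0.05/3)³ = 4.9%. That effect is incidental: the article ties the adjustment to group comparisons, and under the complete null the error with the adjustment is still about 12%. But it is a reason not to delete the adjustment without saying how the scores are handled.

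A reader might also take 16 points as the cost of the plan. That is the Bonferroni case, and no method is named, which an article may fairly leave to a fuller document. A step-down method that uses the fact that at most one pairwise null can be true once the F test has correctly rejected would test at 5% and lose nothing, and would still fit the wording.

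The comparisons with control were sized at 2.5% each, and 168 providers were randomized against 120 in the calculation. At the effects implied there, these comparisons are safe under any of the rules. Adjusted comparisons can also support simultaneous intervals.

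All of this stands as a limit on the size and reach of the point. None of it makes a single-step or Holm adjustment necessary within a score.

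**Conclusion.** The point holds per score. With three groups and the equal-variance ANCOVA model, the gate is sufficient for familywise control within a score, and a further single-step or Holm adjustment can only reduce power. The plan is conservative, not invalid; nothing in it inflates the error within a score.

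The size is conditional on a 5% F test, r = 0.5, the assumed effects and the unnamed method. At 0.4 and 0.6 SD the loss is 9 to 16 points for web versus control and 5 to 11 for supervision versus web under the three adjustments examined. At about 1 SD it is negligible for the comparisons with control. The practical gain is therefore mainly for supervision versus web and for effects smaller than those designed for. Even with the gate alone, supervision versus web has only 15% to 23% power in these scenarios, so the change helps that hypothesis without rescuing it.

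**What to change.** Replace the pairwise sentence in Primary analyses with a rule of this kind: within each technique score, the three-group F test is carried out at the level allotted to that score; if it rejects, the three pre-planned comparisons are each tested unadjusted at that same level. Use the same within-score rule in Secondary analyses.

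Add one sentence on the three technique scores. Either state that error control is claimed per score, or allot the level across the three omnibus tests, for example by Holm. Holm protects the three omnibus conclusions. If all nine pairwise comparisons (three scores × three pairs) are to be covered jointly, a fixed share of 5%/3 = 1.67% per score, used for both the gate and the pairs, does that. This share equals the Bonferroni pairwise threshold above, so the power gain is then given up in exchange for control across scores.

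The cost is a sentence or two and no extra participants. The article describes the study as still blinded, so the change should be dated before unblinding. The downside is that the unadjusted pairwise confidence intervals are not simultaneous, and they should be labelled so.
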